#### 4.4 Control arm

Participants in the control arm will continue with their usual health care. They will be encouraged to take advantage of all available smoking cessation support services offered either through the ACCHS or through Quitline. Although participants in the control group could potentially download the app, they will be unable to successfully register to use it (via a database cross-check). At the end of 6 months follow-up control arm participants will be offered access to the app should they be interested in using it for a minimum 6-month period.

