### Intervention

- (1) A multifaceted smartphone application available on Android or iOS platforms that comprises a personalised profile and quit plan, behavioural strategies to increase motivation to quit and maintain an quit attempt, craving support, and a challenge feature in which users can 'compete' with others on a personalised challenge.
- (2) Usual smoking cessation support provided through either the participating Aboriginal Community Controlled Health Service or the NSW Aboriginal Quitline.

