### Aims

We hypothesise that a multi-faceted intervention using a mobile phone application when combined with usual smoking cessation support services will double smoking abstinence rates at 6 months.

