### 3.3 Objectives

The overall project goal is to develop and evaluate an mHealth intervention to assist Aboriginal people in NSW with smoking cessation assistance. We hypothesise that a multi-faceted smoking cessation mobile application (Can'tEvenQuit), provided as part of routine smoking cessation services, will result in a doubling of biochemically verified smoking abstinence rates at 6 months when compared with usual care.

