### 4.3 Intervention arm

All participants will be free to participate in any other smoking cessation service or support that they wish to use, and will be offered Quitline and local ACCHS contact numbers. Participants allocated to the intervention group will have the opportunity to download and register using the Can'tEvenQuit app immediately. The app will be accessible via the Apple App Store and Google Play. Intervention

arm participants will be able to invite external people to use a simplified version of the app to support participation in a quit smoking challenge.

A support worker will facilitate with registration profile, password set-up and establishing a tailored quit plan. Participants will then be given a tutorial of app feature including how to set up a challenge, motivational support and tracking progress on their plan. App set up can also be done without the use of a support worker if desired. Detailed information about the intervention content, design and features are provided in Appendix 1.

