#### 4.4 Outcomes

The primary outcome is self-reported continuous smoking abstinence, objectively verified at 6 months. Self-reported continuous abstinence is defined as no more than five cigarettes smoked in the past week at 4 weeks follow-up and no more than five cigarettes smoked since the start of the abstinence period at 6 months of follow-up. Self-reported smoking cessation will be confirmed with an Airmet Scientific Micro Plus Smokerlyzer (carbon monoxide metre breath test where a reading of >8 represents recent tobacco smoking). (10)

Secondary outcomes are point prevalence of abstinence (ie, no smoking in the past 7 days) at 4 weeks and 6 months, and self-reported continuous abstinence since the start of the abstinence period, 28-day abstinence, and use of other smoking cessation services (counselling, nicotine replacement therapy, medication) during the trial.

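### Encouragement to use other cessation services is written for the control arm only, so the protocol does not ensure the same cessation background in both arms

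*Protocol*

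**What the plan says.** The question is posed as an add-on comparison. The synopsis (Intervention) has two components, the app and, second, "Usual smoking cessation support provided through either the participating Aboriginal Community Controlled Health Service or the NSW Aboriginal Quitline". The synopsis (Aims) hypothesises that an intervention "using a mobile phone application when combined with usual smoking cessation support services will double smoking abstinence rates at 6 months". Section 3.3 describes the app as "provided as part of routine smoking cessation services, will result in a doubling of biochemically verified smoking abstinence rates at 6 months", compared with usual care.

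The background is then described in two places:

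- **Section 4.3, Intervention arm**, but worded for everyone: "All participants will be free to participate in any other smoking cessation service or support that they wish to use, and will be offered Quitline". The offer also covers telephone numbers for the participant's ACCHS.
- **Section 4.4, Control arm**: "Participants in the control arm will continue with their usual health care", followed by "They will be encouraged to take advantage of all available smoking cessation support services offered either through the ACCHS or through Quitline".

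Section 4.4 Outcomes makes "use of other smoking cessation services (counselling, nicotine replacement therapy, medication) during the trial" a secondary outcome.

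**The concern.** Leaving people free to use services and handing out numbers is permissive. Encouraging them to take up everything available is an active prompt. The protocol writes the first for both arms and the second for controls alone. Staff work from the arm descriptions rather than the statement of aims, so an add-on aim does not by itself secure an equal background.

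Two results are at stake. The first is the abstinence contrast: if controls use more counselling, nicotine replacement or medication because the study prompted them, part of the difference between arms reflects that prompt and not the app. The second is the service-use outcome. Appendix 1 (My Quit Plan) puts information on nicotine replacement and medication, with an adherence tracker, inside the app, so greater service use is a plausible route by which the app works. A prompt to controls alone could hide that signal. The pilot is meant to supply preliminary effectiveness data for a later, powered trial (section 4.6), so a distorted contrast would carry into that trial's planning.

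**Working it through.** **1. The background, arm by arm**

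| Element | Intervention | Control | Source |
|---|---|---|---|
| Free to use other services | yes | yes | 4.3 |
| Quitline and ACCHS numbers offered | yes | yes | 4.3 |
| Usual support named as part of the arm's care | yes | yes | Synopsis, Intervention; 4.4 Control arm |
| Encouraged to use all available services | not stated | stated | 4.4 Control arm |
| Support worker for app set-up and quit plan (optional) | yes | no | 4.3 |
| Telephone call at 1 week about using the app | yes | no | 4.9 |

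The last two rows can be read as delivery of the app. The encouragement row cannot: it concerns the background, and it differs by arm.

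**2. The plan's own figure**

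Inputs from section 4.6: 5% v 10% at 6 months, alpha 0.05, 80% power, 15% loss. Two-sided testing is from section 4.11 and 1:1 allocation from section 4.8.

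n per arm = [1.96 √(2p̄(1−p̄)) + 0.842 √(p₁(1−p₁) + p₂(1−p₂))]² / (p₂−p₁)²

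With p̄ = 0.075 this gives 435 per arm, 870 in total. Then 870/0.85 = 1024, or 870 × 1.15 = 1001. The stated 1000 is reproduced, and this point disputes no sample-size figure.

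**3. Illustration of size (assumptions, not document figures)**

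Let a control-only prompt lead an extra fraction f of controls to use services, and let such use multiply quitting by m. Hold the intervention rate at 10% and assume no change in service use there.

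Control rate = 0.05 × (1 + f(m − 1))

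| f | m | Control rate | Relative risk |
|---|---|---|---|
| 0 | – | 5.00% | 2.00 |
| 0.10 | 1.5 | 5.25% | 1.90 |
| 0.20 | 1.5 | 5.50% | 1.82 |
| 0.20 | 2 | 6.00% | 1.67 |

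The shift is 0.25 to 1 extra quitter per 100 controls. The service-use outcome would carry a difference of 10 to 20 percentage points, but that only restates the assumed f.

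**4. What that would mean for the later trial**

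Evaluable per arm = 500 × 0.85 = 425. Power = Φ(z), where z = [(p₂−p₁)√n − 1.96 √(2p̄(1−p̄))] / √(p₁(1−p₁) + p₂(1−p₂)).

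- 5% v 10%: z = 0.811, power 79%.
- 5.25% v 10%: z = 0.652, power 74%.
- 6% v 10%: z = 0.190, power 58%. The evaluable total for 80% power would be 1442 instead of 870.

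For the pilot's 4-week comparison (12% v 28.8%), power with 85 evaluable per arm is 78%. If the control rate were 14% instead of 12% (again an assumption), it would be 66%.

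**5. The opposite direction**

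The 6% case is a 1.2-fold rise in the control rate (0.06/0.05). If the extra contacts in the intervention arm raised its rate by the same factor, 0.12/0.06 = 2.00 and the relative risk would be unchanged. The documents give no figure for either effect, so the net direction cannot be derived.

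**The case against.** The strongest reply is that this is one sentence without a counterpart, in a protocol that states the add-on contrast several times. Several parts of that reply stand.

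- A reader might infer that intervention participants are only given telephone numbers. The documents do not support this: the numbers go to everyone, usual support is a named component of the intervention, and the app carries treatment information.
- A reader might infer that staff would give controls an extra push once allocation is known. The Control arm section does not say who encourages, when, or from what script. Section 4.9 schedules no control-only contact. The scheduled one-arm contacts after randomisation are all in the intervention arm, and the 4-week call is made by a blinded officer. Participants come from ACCHSs, the Aboriginal Quitline and a screening program, so the encouragement may simply describe usual care there.
- A reader might infer a bias towards no effect. That is one possibility, but the intervention-only contacts could act the other way.
- A reader might call the service-use outcome uninterpretable. That is too strong: health-service use is asked at baseline, 4 weeks and 6 months (section 4.5), and section 4.9 adds a clinic record audit for consenting ACCHS recruits, so an imbalance would be visible.

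What does not stand is the step from these points to no defect. Stating the aim does not equalise the arms, measuring service use describes an imbalance without removing it, and nothing in the protocol extends the encouragement to both arms.

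**Conclusion.** The point holds as an inconsistency between the synopsis and section 4.3 on one side and the Control arm section on the other. As written, the plan does not ensure the same cessation background in both arms, which its add-on question requires. It does not follow that background care will differ, or that the trial cannot isolate the app: the stated contrast is the right one for that purpose, and the defect lies in how the background is worded.

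The size is unknown. The illustrative fall in relative risk from 2.00 to between 1.90 and 1.67 rests wholly on the assumed uptake (10% to 20%), the assumed multiplier (1.5 to 2) and an unchanged intervention arm. The net direction is uncertain. The service-use outcome would be harder to interpret if the text were followed literally. The point is worth correcting because it touches the comparison itself and costs almost nothing to settle before recruitment.

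**What to change.** Reconcile the synopsis (Intervention), section 4.3 and section 4.4 Control arm in one of two ways:

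1. Use one statement about other cessation services that applies explicitly to both arms, delivered from the same script at the baseline contact before allocation is revealed.
2. If the difference is intended, say so and define the comparison as the app versus encouraged usual care, so that the hypothesis and the service-use outcome are read on that basis.

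The content of the message is for the investigators to decide. The cost is protocol and script wording only: no added contacts, staff or procedures, and no change to the sample size.

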#### 4.4 Outcomes

The primary outcome is self-reported continuous smoking abstinence, objectively verified at 6 months. Self-reported continuous abstinence is defined as no more than five cigarettes smoked in the past week at 4 weeks follow-up and no more than five cigarettes smoked since the start of the abstinence period at 6 months of follow-up. Self-reported smoking cessation will be confirmed with an Airmet Scientific Micro Plus Smokerlyzer (carbon monoxide metre breath test where a reading of >8 represents recent tobacco smoking). (10)

Secondary outcomes are point prevalence of abstinence (ie, no smoking in the past 7 days) at 4 weeks and 6 months, and self-reported continuous abstinence since the start of the abstinence period, 28-day abstinence, and use of other smoking cessation services (counselling, nicotine replacement therapy, medication) during the trial.

#### 4.5 Participant timeline

| Assessment Description                                   | Screening | Baseline/
Randomisation/
Enrolment | Visit 1
Telephone
(4 weeks) | Final visit
Face-to-
face
(6 months) |
|----------------------------------------------------------|-----------|------------------------------------------|-----------------------------------|-----------------------------------------------|
| Informed Consent                                         | X         |                                          |                                   |                                               |
| Eligibility                                              | X         | X                                        |                                   |                                               |
| Reasons for non-participation                            | X         | X                                        |                                   |                                               |
| Demographics, Medical History, Medications               |           | X                                        | x                                 | x                                             |
| Questionnaires - Quality of Life, use of health services |           | X                                        | X                                 | X                                             |
| Carbon monoxide metre breath test                        |           |                                          |                                   | X                                             |
| Serious Adverse Events                                   |           | X                                        | X                                 | X                                             |

#### 4.6 Sample size

On the basis of the Text2Quit and Text2Stop trials we estimate the control arm abstinence rate at 6 months to be 5%. Assuming that the abstinence rate is double that of the control arm, we calculate that 1000 participants would be needed to detect a 5% absolute difference (ie: 10.0% vs 5.0%; relative risk 2.00), assuming a 15% loss to follow-up,  $\alpha=0.05$  and 80% probability of detecting a significant difference with p values  $<0.05$  judged as significant. This study will be a pilot RCT in which 200 participants will be recruited to assess feasibility, resource considerations, acceptability and preliminary effectiveness data to inform a future, adequately powered trial.

Using the secondary outcome measure of 7-day abstinence rates at 4 weeks, and assuming the control arm abstinence rate is 12% and the intervention arm abstinence rate is 2.4 times greater (as observed in the Text2Stop trial), there will be 80% probability of detecting a significant difference with 200 participants from the pilot study under the same assumptions as above.

#### 4.7 Recruitment

Recruitment will take place via three settings. Up to four Aboriginal Community Controlled Health Services will be invited to participate in the study. Callers to the Aboriginal Quitline and community members screened at a 1 Deadly Step event will also be invited to participate. Interested individuals will be contacted by the project manager to discuss participation.

#### 4.8 Allocation

Randomisation will be single blinded and conducted through the George Institute's central, computer-based randomisation service. Allocation will be 1:1 intervention versus control using a minimisation algorithm to balance for sex, age and Fagerstrom score for nicotine dependence. Staff involved in data collection and analysis will be blinded to treatment allocation.

#### 4.9 Data collection methods

Eligibility assessment will be done in collaboration with the participating sites. All study instruments are administered by questionnaire (with the exception of the carbon monoxide assessment at the end of study.) Baseline data collection, consent and randomisation will be conducted by telephone or via a face to face visit with a trained project officer from the George Institute. For participants allocated to receive the Can'tEvenQuit app, a text message will be sent to the participant's phone with instructions on how to download the app. Participants will then have the option of a self-guided assessment to setting up the app or will be invited to meet with a research staff member to have a face-to-face visit to assist with app installation and set-up. All participants allocated to the intervention will be telephoned at 1 week to determine if they need any support with using the app. There will also be a "contact us" number in the app itself to call for help. At 4 weeks an "evaluation" project officer who is blinded to allocation status will conduct an outcome assessment by telephone for all participants in the trial. At 6 months post randomisation, this officer will conduct the final outcome assessment and biochemical verification of smoking status as part of a face-to-face visit.

In addition to the formal outcome assessment visits an analytic tool built in the app will assess usage patterns, which app features are used and any changes in usage patterns over time. A clinic record audit of smoking cessation support services will also be conducted for consenting participants recruited through ACCHSs.

An automated de-identified data extraction tool will also be provided to participating ACCHSs to assess smoking prevalence, recording rates and provision of smoking cessation assistance at the beginning and end of study for the entire regular client population to assess any changes during the trial period based on methods used previously.(11)

#### 4.10 Data management

Non-electronic study data will be stored securely at The George Institute with access restricted to the principal investigators and the data management staff member responsible for maintenance of the database. Signed participant consent forms will be stored in the Investigator Site Folder at the participating health service. At the completion of the trial the consent forms will be brought back to The George Institute to be filed with essential study documents for 15 years. The investigator shall retain and preserve one copy of all data generated in the course of the study, specifically including but not limited to those documents defined by Good Clinical Practice as essential documents, for 15 years following study closure.

#### 4.11 Statistical Methods

Intention-to-treat principle will be followed, and characteristics will be compared between the groups at 4 weeks and 6-month follow-up using  $\chi^2$  tests for categorical variables and t-tests for continuous variables. Results will be reported in terms of relative risks, 95% CIs and two-sided p values. Analyses will be undertaken using SAS Enterprise Guide (version 5.0). For the pilot study no sub-group analyses will be pre-specified.

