### Randomisation

Centrally performed web-based 1:1 allocation to the intervention versus usual smoking cessation services using a permuted block sequence stratified by study centre, gender and age (Figure 1)

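### The protocol fixes unadjusted tests although allocation is balanced on baseline factors, so the results will be slightly conservative; adjusting for those factors is a cheap, optional improvement

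*Protocol*

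**What the plan says.** Section 4.11 is the protocol's only analysis text. It names χ² "tests for categorical variables and t-tests for continuous variables" at 4 weeks and 6 months, and adds: "Results will be reported in terms of relative risks, 95% CIs and two-sided p values". It mentions no covariate and no stratification.

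Allocation is described in two places, and they differ:
- Section 4.8: a "minimisation algorithm to balance for sex, age and Fagerstrom score for nicotine dependence".
- Synopsis, Randomisation: a "permuted block sequence stratified by study centre, gender and age".

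The timeline in section 4.5 schedules "Questionnaires - Quality of Life, use of health services" at baseline, 4 weeks and 6 months. Baseline values of these questionnaires will therefore exist. Quality of life is not among the outcomes in the Synopsis or in the Outcomes section, all of which concern abstinence or use of cessation services.

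**The concern.** Balancing the arms on a prognostic factor removes the part of the between-arm variation that comes from that factor. A plain χ² test or t-test computes its error as if allocation had been simple, so it still counts that variation. The estimate is then more precise than its reported standard error, the interval is too wide and the p-value too large. Any imbalance that remains by chance also stays in the estimate.

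This bears on a pilot whose stated products include preliminary effectiveness data for a larger trial, and which claims 80% power for a 4-week comparison. The protocol is not silent here: it names unadjusted tests. The point is therefore about a stated choice, not about detail left to an analysis plan.

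**Working it through.** **Inputs from the protocol (section 4.6).** At 6 months, "10.0% vs 5.0%; relative risk 2.00". At 4 weeks, a 12% control rate and a ratio of 2.4, so 0.12 × 2.4 = 28.8%. Two-sided α of 0.05, 80% power, 15% loss and 200 participants. The protocol does not give the prognostic strength of the allocation factors, so it is assumed below over a range.

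**The plan's own figures reproduce approximately.** The formula, with pooled variance under the null and p̄ the mean rate, is n per arm = [1.96√(2p̄(1−p̄)) + 0.842√(p₁(1−p₁) + p₂(1−p₂))]² / (p₂−p₁)².
- 5% vs 10%: [1.96 × 0.3725 + 0.842 × 0.3708]² / 0.05² gives 435 per arm, or 870 in total. 870 / 0.85 = 1,024 and 870 × 1.15 = 1,001, against 1,000 stated.
- 12% vs 28.8%: power is 84.4% with 100 per arm and 78.1% with 85 per arm (after 15% loss), against 80% stated.
- The pilot's power at 6 months is 26.7% with 100 per arm and 23.4% with 85.

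**Simulation 1.** 200 participants without loss; minimisation on sex (2 levels), age (2) and Fagerstrom (3) with a biased coin of 0.8; 3,000 runs per scenario. The unadjusted χ² test is compared with a logistic model containing the factors, standardised to a risk difference. Assumed log-odds per level (sex, age, Fagerstrom) are mild 0.2, 0.3, −0.4; moderate 0.4, 0.6, −0.8; strong 0.8, 1.0, −1.5. Results at 4 weeks, unadjusted → adjusted:

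| Assumed strength | Type I error, % | Power, % | Gain, points |
|---|---|---|---|
| none | 4.7 → 4.8 | 84.0 → 84.3 | 0.3 |
| mild | 4.5 → 4.7 | 85.2 → 85.7 | 0.5 |
| moderate | 4.4 → 4.9 | 86.1 → 87.7 | 1.6 |
| strong | 3.6 → 5.0 | 87.8 → 91.8 | 4.0 |

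The mean unadjusted standard error is 0.0553 in all four rows. The true sampling SD is 0.0542 (moderate) and 0.0505 (strong), so the reported error is too large by factors of 0.0553/0.0542 = 1.02 and 0.0553/0.0505 = 1.10. The Monte Carlo error of such an SD is about 0.0542/√6,000 = 0.0007. The moderate gap of 0.0011 is therefore only about 1.6 Monte Carlo errors, while the strong gap is clear. The adjusted estimate's own SD is barely smaller (0.0540 and 0.0497). Minimisation has already delivered most of the precision, and adjustment mainly lets the analysis report it.

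At 6 months, power goes from 27.2% to 27.6% (mild) and from 26.0% to 27.5% (moderate). Adjusted type I error is 4.8% and 5.4%, with a Monte Carlo error of √(0.05 × 0.95/3,000) = 0.4 points.

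**Other simulations, 170 analysed.**
- Log-odds 0.3, 0.3, −0.5: 4-week power 80.7% → 81.1%. Log-odds 0.3, 0.5, −0.8: 80.4% → 82.3%.
- Unadjusted against adjusted score test, weak to moderate strength, 2,000 runs: 4-week type I error 4.2–4.3% against 4.6–5.2%, and power 79–80% against 81–82%. Power at 6 months is about 24% against 25–26%.

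**The form of the test at 6 months.** Expected events are 85 × 0.05 + 85 × 0.10 = 4.25 + 8.5 = 12.75, about 13. With the log-odds of the first item above (weaker, stronger), power was:
- χ² test: 22.4%, 23.2%
- Wald test of the Mantel-Haenszel relative risk: 16.3%, 17.5%
- modified Poisson: 17.4%, 18.5%, with a failed fit or an empty cell in 1.6% to 2.5% of runs

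The median SE of the log relative risk, unadjusted against Mantel-Haenszel, was 0.593 against 0.593 (weaker) and 0.593 against 0.587 (stronger). The interval narrows by 0 to 1%. The loss of power comes mainly from replacing a score test by a Wald test, and it disappears with a stratified or adjusted score test.

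**The case against.** The case for leaving the text alone is a good one. The unadjusted test is valid, it errs on the safe side, and this is a pilot that says it is not adequately powered. Under weak assumptions the difference is close to nothing. Section 4.11 is a short summary, and an analysis plan that is not shown could add adjusted analyses. At 6 months there are too few events for several covariates, and a careless change to a model-based Wald test would lose power on the primary outcome. All of this stands as to weight. It does not remove the point that the one named method ignores the factors on which the trial allocates.

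A reader might infer three stronger things that the protocol does not support:
- *That the planned tests are invalid or inflate false positives.* In every scenario above for which type I error was computed with assumed prognostic factors, the unadjusted error was below 5% at 4 weeks and 6 months in simulation 1, and 4.2–4.3% at 4 weeks in the score-test comparison.
- *That substantial precision is lost.* Adjusting a continuous score for its baseline value cuts residual variance by r², which is 9% to 49% for an assumed r of 0.3 to 0.7. No listed outcome is such a score. Quality of life appears only as a questionnaire row in section 4.5, so these figures should not drive severity.
- *That any adjustment helps the primary outcome.* The gain there is small and depends on the form of the test.

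**Conclusion.** The point holds as an optional, low-cost improvement. With assumed weak to moderate prognostic strength, the unadjusted tests give up about 0.5 to 3 points of power at 4 weeks and about 0.5 to 2 points at 6 months. Only under strong assumed factors does the 4-week loss reach about 4 points. The error is conservative. All these sizes rest on assumed prognostic strength and on minimisation as in section 4.8. Blocks stratified as in the Synopsis were not simulated, although the same reasoning applies to them. The 6-month comparison stays at roughly a quarter power with either analysis.

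**What to change.** 1. Reconcile the Synopsis with section 4.8 on the allocation method and its factors, because this decides what enters the model.
2. At 4 weeks, make the main comparison a relative risk with 95% CI adjusted for the agreed factors, by standardised logistic regression or modified Poisson with robust errors. Age, and Fagerstrom score if it is a factor, can enter as continuous terms. Expected events are 85 × 0.12 + 85 × 0.288 = 34.7, so the number of terms should stay small.
3. For the 6-month primary outcome, use a Cochran-Mantel-Haenszel (score) test with a Mantel-Haenszel relative risk and 95% CI over one key allocation factor, named in advance. Do not rest the p-value on a Wald test from a multi-covariate model.
4. Keep the unadjusted χ² test as supportive at both times.
5. Where a continuous questionnaire score is compared, use ANCOVA with its baseline value in place of the t-test.

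The cost is a few sentences and a little programming. No new data are needed, since the allocation factors must be known at randomisation and quality of life is already scheduled at baseline. The limit is that about 13 events at 6 months allow little adjustment.
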